### Intervention

The intervention consists of three subcutaneous racemic ketamine doses at weekly intervals and four sessions of CBT (one at commencement of the intervention and three within 24–28 hours following each ketamine administration session) (see figure 2).

**Figure 2 F2:**

Intervention schedule.

#### Medication

The medication under investigation is the Therapeutic Goods Association (TGA)-approved ketamine 100 mg/mL, available in Australia as a liquid solution formulated for intravenous and intramuscular injection as an anaesthetic agent.^41 42^ A total of three subcutaneous subanaesthetic doses, at least 7 days apart, will be administered by a study nurse to the abdomen once weekly during clinic visits at weeks 2, 3 and 4. The starting dose will be 0.75 mg/kg, increased to a maximum dose of 0.9 mg/kg at subsequent visits as tolerated. The dose can be reduced to 0.6 or 0.5 mg/kg if not tolerated (see table 2).

**Table 2 T2:** Study drug schedule

Ketamine 1	Tolerability	Ketamine 2	Tolerability	Ketamine 3
0.75 mg/kg	Well tolerated	0.9 mg/kg	Well tolerated	0.9 mg/kg
			Moderately tolerated	0.9 mg/kg
			Poorly tolerated	0.75 mg/kg
	Moderately tolerated	0.75 mg/kg	Well tolerated	0.75 mg/kg
			Moderately tolerated	0.75 mg/kg
			Poorly tolerated	0.6 mg/kg
	Poorly tolerated	0.6 mg/kg	Well tolerated	0.6 mg/kg
			Moderately tolerated	0.6 mg/kg
			Poorly tolerated	0.5 mg/kg

Tolerability will be assessed by the study doctor guided by the Ketamine Side Effect Tool (KSET),^43^ with the clinician assigning tolerability prior to discharge based on subjective participant reports and objective observations.^43 44^ Acceptable safety and tolerability profiles have been demonstrated in subcutaneous doses of up to 0.9 mg/kg.^44^ The study nurse will continuously monitor the participant at 120 min post ketamine administration and alert the principal investigator or appropriately qualified delegate in the case of any adverse event of concern, which will be managed according to clinical need (eg, conservatively, continued support for up to a further 120 min).

#### Psychotherapy

The four-session manualised CBT programme developed by Baker *et al*^45^ will be provided by trained therapists to all participants in the trial, with adaptations suitable for the KAP approach. Adaptations are specified in a therapist manual developed specifically for the study (unpublished), detailing ‘set and setting’ considerations within this context, preparation sessions (ie, dosing day discussions including intention-setting, grounding exercises facilitated by the therapist and study nurse) and integration discussions (ie, discussions framing each CBT session in relation to ketamine experiences). For the purposes of this study, therapists are defined as staff with qualifications in a relevant health discipline (such as counselling, nursing, social work, psychology, psychiatry) that have undergone training on the use of the CBT manual and in ketamine-assisted psychotherapy adaptations (2.5-hour training session facilitated by a senior clinical psychologist with experience in CBT and psychedelic-assisted therapy for MAUD). Each psychotherapy session will last approximately 1.5 hours. The initial assessment will take place as part of psychotherapy session 1, reviewing: (1) alcohol and other drug use history, (2) mental health assessment, (3) participant’s readiness to change methamphetamine use, and (4) information about what will happen during the first ketamine dose session. One week later, a preparation session will be undertaken immediately prior to ketamine dose 1. Psychological preparation and pre-injection relaxation exercises have been previously shown to reduce the anxiety and distress that might emerge with ketamine administration.^46^ As in previous studies,^32 47 48^ participants will be guided through grounding exercises (eg, relaxation and breathing) prior to ketamine administration and encouraged to use these should any discomfort or anxiety emerge. As part of preparation, study participants will be briefed on what to expect after drug administration and given the opportunity to ask any questions they may have, and a discharge information sheet will be provided. Within 24–48 hours following ketamine dose 1, psychotherapy session 2 will be undertaken, beginning with an integration focus where experiences of the ketamine administration will be briefly explored and used to guide the subsequent CBT material. This approach will also be used for the remaining sessions. Therapists will co-ordinate the four sessions to occur at least 1 week apart. Session 1 will occur during week 1; sessions 2, 3 and 4 will occur during weeks 2, 3 and 4 respectively within 24–48 hours of participants receiving study medication. Session checklists will be completed post-session by the therapist to assess treatment fidelity and discussed during group supervision with a senior psychologist. As per Baker *et al*,^45^ study participants will be encouraged to complete homework tasks in-between sessions.

### Outcomes

The primary outcomes of this pilot study are safety and feasibility. Safety will be assessed by treatment emergent adverse events (AEs) across the duration of the study, categorised by system organ class (SOC). These will be described by seriousness, severity, causality and expectedness.^49 50^ AEs will be documented at each clinic visit. Subjective descriptions of AEs provided by participants will be transcribed verbatim and reported in accordance with the Medical Dictionary for Regulatory Activities (MedDRA) terminology, developed under the auspices of the International Council for Harmonisation of Technical Requirements for Pharmaceuticals for Human Use (ICH). Severity will be graded from grade 1 (mild) to grade 5 (death) by the site principal investigator.^51^ Causality will be determined by the site principal investigator, and expectedness in accordance with international guidelines and Australian product labels for ketamine hydrochloride 100 mg/mL for injection.^41 42^ Any known reaction listed on the product label will be considered potentially causally related. Adverse events will be elicited through structured assessment with the KSET.^43^ Additional safety measures (see online supplemental file 3 for administration timepoints) include: (i) blood pressure and heart rate during ketamine administration sessions, (ii) dissociative effects as measured by the Clinician-Administered Dissociative States Scale (CADSS-6),^52^ (iii) elevated mood as measured by the Young Mania Rating Scale (YMRS [item 1]),^53^ (iv) suicidality as assessed with the C-SSRS, (v) non-medical use liability as measured by the Drug Effects Questionnaire (DEQ-5),^54 55^ and (vi) changes in other drug use (including ketamine) as measured by Timeline Follow Back (TLFB).^56^

Feasibility will be assessed by: (i) time taken to recruit the sample (with a 12-month study timeframe imposed, based on unpublished studies from our group in similar contexts successfully recruiting 20 participants within this timeframe); (ii) proportion of ineligible participants at pre-screening and screening; (iii) number of participants who receive three doses of ketamine, (iv) number of participants who complete four sessions of psychotherapy, (v) retention rate over the full duration of the study, and (vii) acceptability of the intervention, assessed via qualitative interviews. As this is the first study of its kind in this population and pilot studies are not generalisable to other contexts,^57 58^ these will be assessed and reported descriptively. While we conservatively anticipate 50% completion of 4 sessions of CBT and 75% completion of 6-month follow-up assessments based on studies of CBT in this population,^13 59^ these are not directly comparable given the pharmacotherapy component of the present study design. Therefore, results will be synthesised in consideration of the feasibility to progress to larger studies, taking into account the measures described above and, equally so, the qualitative acceptability.^60^

Secondary outcomes include measures of preliminary efficacy and potential mediators. These measures include: (i) self-reported change in the past 28 days of MA use from baseline to week 5 (post treatment), week 8 (primary endpoint), week 12 and week 24 as measured by the TLFB,^56^ (ii) presence of methamphetamine in urine assessed through POC UDS at week 5, week 8, week 12 and week 24, (iii) changes in methamphetamine craving as measured by the Visual Analogue Scale-Craving (VAS-C)^61^ and withdrawal symptoms assessed on the Amphetamine Withdrawal Questionnaire (AWQ)^62^ from baseline to week 5, week 8, week 12 and week 24, (iv) changes in quality of life as measured by the WHO Quality of Life-Brief Version (WHOQOL-BREF)^63^ from baseline to week 5, week 8, week 12 and week 24, and (v) treatment satisfaction as measured by the Treatment Satisfaction Questionnaire for Medication (TSQM-II)^64^ and the Client Satisfaction Questionnaire (CSQ-8)^65^ at week 5 and week 8.

Potential mediator measures are changes in: (i) depression scores on the Patient Health Questionnaire-9 (PHQ-9)^66^ from baseline to week 5, week 8, week 12 and week 24, (ii) anxiety scores on the Generalised Anxiety Disorder Scale-7 (GAD-7)^67^ from baseline to week 5, week 8, week 12 and week 24, (iii) emotion regulation scores on the Difficulties in Emotion Regulation Questionnaire (DERS)^68^ from baseline to week 5, week 8, week 12 and week 24, (iv) sleep quality scores on the Insomnia Severity Index (ISI)^69^ from baseline to week 5, week 8, week 12 and week 24, (v) HIV and other sexually transmitted infection risk behaviours as measured by the Substance Use Sex Index (SUSI)^70^ from baseline to week 5, week 8, week 12 and week 24, (vi) subjective medication effects on the Hood Mysticism Scale (HMS)^71^ 120 min post ketamine administration, (vii) cognitive control and flexibility as measured by the Emotional N-back task^72^ at baseline and 24 hours post third ketamine administration, and (viii) cognitive control as measured by the Emotional Stroop task^726^ at baseline and 24 hours post third ketamine administration.

### Sample size

The study is not powered to determine efficacy. The study will recruit 20 participants, as is convention in pilot studies.^73^

### Participant retention and withdrawal

The study site will make all reasonable efforts to follow participants for the course of the study. Efforts to minimise loss to follow-up will include respecting participant time commitments, formal tracking procedures including multiple ways to be contacted and strong interpersonal skills of study personnel.

#### Stopping criteria

If a participant experiences a grade 3 or grade 4 adverse event (AE) considered to be causally related to the study medication, no further study medication will be dispensed until the participant has been reviewed by the site principal investigator.^51^ If the AE is resolved to the satisfaction of the principal investigator, the dose can be recommenced, and the participant will be reviewed the subsequent day. If the AE is not resolved or recurs after recommencing the study medication, the site principal investigator will consider ceasing the medication and withdrawing the participant from the treatment component of the study. Unless they revoke their consent, all participants withdrawn from treatment will continue to be followed as intention to treat.

#### Reimbursement

Participants will be reimbursed for participating, in accordance with Australian guidelines for appropriate and equitable payment of participants in research.^74^ Participants who consent to partake in the study and complete all the screening assessments will receive a $40 gift card. Reimbursements of $40 gift cards will also be made for each study visit. If the participant chooses to have their qualitative interview scheduled for the same day as another visit during weeks 5 to 8, they will still receive a separate $40 reimbursement for the interview. The maximum potential amount of reimbursement over the entire duration of the study is $520 of gift cards per person.

### Data management

Study data will be collected and managed using REDCap (Research Electronic Data Capture) tools hosted at St Vincent’s Hospital, Sydney.^75^ REDCap is a secure, web-based software platform designed to support data capture for research studies, providing (i) an intuitive interface for validated data capture, (ii) audit trails for tracking data manipulation, (iii) automated export procedures for seamless data downloads to common statistical packages, and (iv) procedures for data integration and interoperability with external sources. In accordance with the National Standard Operating Procedures for Clinical Trials,^76^ identifiable information will be stored separately from the main study data. The Participant Identification Log will be stored in a password-protected folder on a secure SVHS hosted server. Access to study records within the REDCap database will be limited by using Data Access Groups (DAGs). Only users within a given DAG can access records created by users within that group. Access to components of study records is role-based and can only be granted by the project manager. Data will only be made available to investigators who are directly involved in the collection, analysis or monitoring of study data. Following conclusion of the study, physical and digital records will be stored for a period no less than 15 years as per ICH-GCP guidelines.^49^

### Statistical methods

Descriptive statistics will be used to characterise the study sample. Quantitative analyses will be descriptive and exploratory and include basic measures of central tendency, CIs around means or proportions, Cohen’s d, and paired sample t-tests to assess pre-post intervention changes. P values are considered preliminary and will be reported with caution, supplemented with appropriate metrics (eg, CIs). For categorical measures such as the presence of AEs, rates will be analysed using appropriate non-parametric approaches, such as χ² and relative risk. Quantitative data will be analysed using SPSS Version 29.0.^77^ Qualitative interviews will be collected until all trial participants have been approached. Interviews will be thematically analysed to extract key themes across participant responses, using the approach outlined by Braun & Clarke^78^: familiarising with the data, generating initial codes, searching for themes, reviewing themes, defining and naming themes, and producing the report. Qualitative data will be analysed using NVivo Version 14.^79^

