**Protocol version:**

The trial protocol (Version 4.0) was approved on 24 June 2024.

STRENGTHS AND LIMITATIONS OF THIS STUDYThe KAPPA pilot study is the first to examine the safety and feasibility of ketamine-assisted psychotherapy for methamphetamine use disorder.Structured clinical intervention of standardised manual-based cognitive behavioural therapy alongside a rigorous low-cost subcutaneous racemic ketamine dosing protocol allows for ready reproducibility.Moving beyond abstinence, the study tests the feasibility of measuring validated secondary outcomes that align with harm-reduction and person-centred approaches, including reduction in methamphetamine use and improved quality of life.A strength of the study is the use of structured clinical interviews to screen and characterise the sample.There is a risk of high attrition rates over the course of the study.

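### Paired t-tests estimate week-24 change only in participants who attend that visit, about 15 of 20 on the protocol's own expectation, and ignore the earlier visits of those lost

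*Protocol article*

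**What the plan says.** The Objectives and Outcomes sections ask for change from baseline to weeks 5, 8, 12 and 24 in methamphetamine use, craving, withdrawal and quality of life, with several mediator scales on the same schedule. For these the Statistical methods section names "paired sample t-tests to assess pre-post intervention changes", with confidence intervals and Cohen's d. It names no other method for change over time. The same section states that "Quantitative analyses will be descriptive and exploratory" and treats p values as preliminary.

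Under Sample size, "The study will recruit 20 participants, as is convention in pilot studies" and "The study is not powered to determine efficacy". On retention, the Outcomes section anticipates "75% completion of 6-month follow-up assessments based on studies of CBT in this population", then adds that "these are not directly comparable given the pharmacotherapy component of the present study design". The strengths and limitations box says "There is a risk of high attrition rates over the course of the study". The Stopping criteria section adds that, unless they revoke consent, "all participants withdrawn from treatment will continue to be followed as intention to treat".

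**The concern.** A paired t-test drops anyone without the later value. Run separately at four follow-up visits, it may describe a different subset of participants each time. A participant seen at weeks 5, 8 and 12 but lost by week 24 is absent from the week-24 estimate, although the earlier visits say a good deal about how that person was doing.

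The trial has one arm, so within-person change is its only signal of preliminary efficacy. Reporting p values with caution does not help here, because selective loss shifts the mean change and Cohen's d themselves. At stake is an exploratory effect size that a reader may carry into the planning of a later randomised trial.

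**Working it through.** **Inputs from the protocol.** N = 20 (Sample size). Anticipated completion at 6 months is 75% (Outcomes). The paired t-test is the named method (Statistical methods). The protocol gives no expected change, standard deviation (SD) or correlation, and no expected loss at weeks 5, 8 or 12. The sample size rests on convention, so there is no calculation to reproduce.

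**Number of pairs.** 20 × 0.75 = 15 pairs at week 24, with 5 participants outside the test. The 95% binomial range is 11 to 18 pairs.

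**Precision.** The half-width of the 95% CI for a mean change, in SDs of change, is t(0.975, n−1)/√n. It is 0.47 at n = 20 and 0.55 at n = 15.

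**Bias formula.** Whole-sample change = 0.75 × (change in attenders) + 0.25 × (change in those lost). The bias of the complete-pair mean is therefore 0.25 × (attenders − lost).

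- With no gap between the groups, the bias is 0.
- Assumed gaps of 0.5, 1.0 and 1.5 SD give 0.125, 0.25 and 0.375 SD.
- If attenders cut 8 days of use and those lost cut none, the true mean is 0.75 × 8 = 6 days, while the paired test reports 8. This is a third too large (1/0.75 = 1.33) and assumes that every lost participant is unchanged.

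**Simulation in days of use (all inputs assumed).** Means were 18, 13, 12, 12.5 and 13 days at baseline and weeks 5, 8, 12 and 24. The SD was 7, the correlation between any two visits 0.6, and 25% were lost by week 24. The true week-24 change is 13 − 18 = −5.0.

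| Loss depends on | Complete pairs | Likelihood estimate, all visits |
|---|---|---|
| last observed change (three strengths) | −5.60, −5.94, −6.22 | −4.93, −4.88, −4.96 |
| level of use | −4.6 to −4.8 | – |

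In the first row, 5.60/5 = 1.12 and 6.22/5 = 1.24, so the complete-pair estimate is 12 to 24% too large. In the second row it is 0.2 to 0.4 days too small, so the direction reverses.

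**Second simulation (SD units, N = 20, correlation 0.6, true change −0.50, 25% lost).** The comparison estimate uses every participant's baseline and week-8 values.

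| Loss depends on | Complete pairs, mean (SD) | Using all participants, mean (SD) |
|---|---|---|
| nothing (random) | −0.50 (0.231) | −0.50 (0.227) |
| week-8 change, moderately | −0.589 (0.229) | −0.502 (0.234) |
| week-8 change, strongly | −0.635 (0.227) | −0.500 (0.247) |
| week-8 level, strongly | −0.500 (0.233) | −0.501 (0.246) |

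Here the excess under change-dependent loss is 0.089/0.5 = 18% to 0.135/0.5 = 27%, of the same order as before. The exact size moves with the assumed dropout model.

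Root mean squared error combines bias and spread. Under strong change-dependent loss it is √(0.135² + 0.227²) = 0.264 for complete pairs, against 0.247 for the estimate using all participants. Under level-dependent loss there is no bias, and the estimate using all participants is slightly noisier (0.246 against 0.233).

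**Third simulation.** With a random-intercept likelihood model as the comparator, complete pairs gave about −5.9 and the model −5.0 (truth −5.0) under change-dependent loss. The two agreed when loss was random or depended on level. The model's error was equal or smaller in every scenario, and clipping the data to 0–28 days did not alter this.

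**The case against.** **Missing-data handling belongs in an analysis plan that is not shown.** This is right as far as it goes: the list of methods is not worded as exhaustive, and the absence of an imputation rule is no error. The paired t-test, however, is a stated choice, and it settles who enters the estimate.

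**The analyses are exploratory.** This stands. The study is not powered for efficacy, and the Outcomes section bases progression to larger studies on the feasibility measures and, equally, on qualitative acceptability. It limits the weight of the point without removing it.

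**The bias is small against the noise.** In the simulation in days, the bias of 0.6 to 1.2 days is below the sampling SD of the complete-pair estimate (1.5 to 1.7 days). This is true for a single trial of 20, and the inputs are assumptions. The error is nonetheless systematic and can be reduced with data already collected.

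**Three stronger readings a reader might infer are not supported.**

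- *That the t-test contradicts the intention-to-treat sentence.* That sentence keeps people who stop treatment in follow-up. It sets no analysis population and no missing-data rule. Those who stop treatment but attend the visit are in the paired test.
- *That a quarter is lost at every visit.* The 75% applies to 6 months only and comes from studies the protocol calls not directly comparable. No loss is stated for week 8, which the protocol labels the primary endpoint.
- *That attenders must overstate improvement.* People using heavily may well be the likeliest to be lost, but loss driven by level of use gave no bias or a reversed one in the simulations.

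**Conclusion.** The point holds as a limited one. As written, the week-24 change and its Cohen's d would rest on about 15 of 20 participants, and the earlier visits of those lost would go unused. Whether this biases the result depends on why people are lost. Loss that follows a participant's own change in use makes the estimate too favourable, by roughly 12 to 24% under the assumed inputs. Random loss does no harm, and loss that follows level of use may leave no bias or reverse it. These sizes rest on an assumed SD, correlation, true change and dropout model, none of which the protocol gives. The safety and feasibility outcomes do not depend on this analysis.

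**What to change.** For each continuous outcome measured at baseline and weeks 5, 8, 12 and 24, replace the separate paired t-tests with one likelihood-based linear mixed model:

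- All five visits are responses, visit is a categorical fixed effect and participant a random effect. All enrolled participants with any data are included.
- Report the change at each visit with a 95% CI, and Cohen's d as the model estimate divided by the baseline SD.
- For days of use in the past 28, which are bounded at 0 and 28, add a confidence interval from a bootstrap that resamples participants.
- Give the number observed at each visit.
- Add one sensitivity analysis that sets missing values to no change from baseline. With 15 of 20 observed, this multiplies the observed mean change by 0.75.

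The cost is a little more analysis of data already being collected. The model relies on data being missing at random given the observed visits, which cannot be verified; the sensitivity analysis shows how far one unfavourable departure would move the result. The confidence interval may be slightly wider: in the simulation in days, the estimate's SD across trials was 1.6 to 1.75 days, against 1.5 to 1.7 for complete pairs.
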